### Criteria for discontinuing or modifying the interventions

If a PR staff member is unable to attend any part of their training, an alternative session will be provided, if possible, at another training session. If a staff member is unable to continue in the trial, another PR staff member who has attended training will take over the role. If a PR buddy is unable to attend any part of the training, the component(s) missed will be noted and, where possible, catch-up sessions will be arranged. If missed training sessions cannot be caught up, the volunteer(s) will be signposted to other volunteering opportunities.

Following training, if a PR buddy is unable to continue supporting patients the patients will be allocated a different PR buddy. If a PR buddy asks to be withdrawn from support of a particular patient participant, or a patient participant asks to be withdrawn from receiving support from a particular PR buddy, the party seeking to be withdrawn will be interviewed by a PR staff member to assess the issue. If there are no concerns about the behaviour of the other party, then the staff member will recommend that new PR-buddy support or a new patient participant will be found to replace the withdrawing party.

### Strategies to improve adherence to interventions

Attendance registers will be kept for both PR-staff and PR-buddy training. Checklists will be used to record the required elements of the training delivered. Each remote live day of PR-staff training and at least 1 session (1/4 of a day) of the PR-buddy training at each site will be recorded by the IMPROVE research team to enable more objective assessment of fidelity of delivery of training. A 20% sample will be analysed for content of delivery by listening back to of these recordings and comparing them to the relevant component of the training manual and slide deck. Training reviews will be used both for PR staff and PR buddies to assess fidelity of receipt of the training.

Using dedicated trial phones, PR buddies will record the contacts they have with the patients they support. Recordings will be collected once a month by the research team. Intervention fidelity of PR-buddy support will be assessed by listening to a randomly selected sample of the recordings (10% of the recordings made by 2 PR buddies per site). This assessment will focus on analysing delivery style (use of communications skills training) and on the use of taught behaviour change techniques by the PR buddies. Analysis will be based on a coding framework developed and used in the feasibility study [25]. Recordings will be coded independently by two coders and discrepancies in coding then resolved by discussion.

Any concomitant care is permitted. It is not anticipated that provisions will be required for post-trial care. This trial has been assessed as low risk. The trial co-sponsors have agreed that any harm resulting from the trial will be the responsibility of the main sponsor, King’s College London. King’s College London will provide indemnity for the duration of the trial.

### Outcomes

The primary outcome is completion of PR by each individual patient participant, summarised as a proportion for each trial site. Standard PR treatment usually consists of a pre-PR assessment, twelve classes over 6 to 8 weeks and a final assessment. Uptake is defined as attendance at the pre-PR assessment; completion is defined as attendance of 75% or more of the planned PR sessions—usually at least 9 out of 12 sessions [31, 32].

The secondary outcomes are:The proportions of PR sites that were recruited and that were retained—measured through a site recruitment log and a record of withdrawal/default.Demographic and clinical characteristics of PR buddies in participating sites measured through data collected and recorded on the PR-buddy application form.The proportions of patient participants that were recruited and retained—measured through a site log rate of acceptance of the invitation to participate, rate of assessment for PR and rate of participants followed through to completion.Demographic and clinical characteristics of patient participants in participating sites measured through data collected and recorded on Case Report Forms (CRFs) at recruitment and consent interview.Exercise capacity being assessed at the pre-PR assessment, respiratory-specific quality of life and psychological wellbeing measured at baseline, at 3 months and at 6 months in a questionnaire. Exercise capacity will be measured through site records of the 6-min walking distance test or the incremental shuttle walk test or the 60-s sit to stand test [33–35]. Quality of life and psychological wellbeing will be measured by the Chronic Obstructive Pulmonary Disease Assessment Test and the Hospital Anxiety and Depression Scale in a postal questionnaire [36, 37]. Breathlessness will be measured by the Medical Research Council breathlessness questionnaire [38].

The process evaluation will include collection of process data (e.g. relating to training delivery, contacts between PR buddies and supported patients), qualitative interviews with some of the trial participants (PR staff and patient participants), focus groups with some PR buddies and field diaries to capture reflections of researchers throughout the implementation period. Assessment of the fidelity of the intervention delivery of patient support by PR buddies is as described above. We will also perform an economic evaluation to examine whether the intervention is potentially cost-effective compared to the current standard care alone, from the perspectives of the NHS and personal social services and the society.

### Participant timeline

Figure 1 (Spirit Figure) shows the timeline for enrolment and participation in the study. PR sites, PR buddies and patient participants will be enrolled for approximately 9 months.

**Fig. 1 Fig1:**
[figure not shown]
Timeline of participation in the study (Spirit Figure)

### Sample size

Based on the 2017 PR audit of the Royal College of Physicians the mean completion proportion over 182 PR sites in England was 40% [12]. Sites with a completion proportion of 55% or less were considered “sub-optimal performers”; the mean completion proportion among these sites was estimated at 32%. Due to regression to the mean, it is likely that these “sub-optimal” performing sites may perform better the following year, and so the control group completion proportion is likely to be between 32 and 40%.

Assuming an overall completion proportion of 40% in the control group, 36 sites (18 per arm) would be required to detect a 40% relative increase in completion proportion to 56% with 90% power, assuming an intraclass correlation coefficient (ICC) of 0.056 and 30 patient participants per site. The choice of ICC = 0.056 was made on basis of the literature and recommendations based on similar interventions [39]. Where interventions include training of health professionals, or other personnel who will deliver the intervention while the outcome is to be measured on patients, an ICC around 0.05 has been widely used. Assuming a completion proportion of 32%, the same number of sites would also be required to detect an increase from 32 to 48%, assuming the same power and ICC. Therefore, after accounting for one site per arm dropping out, a total of 38 sites (19 per arm) would be required. After accounting for six (20%) patient participants dropping out, 36 patient participants would be required in each site.

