### Trial design

IMPROVE is a prospective, open, pragmatic, cluster randomised controlled clinical trial, with an internal pilot, with clustering at site level. Sites will be PR services. The feasibility study suggested that the recruitment and training of PR buddies and the recruitment of patient participants are feasible [26]. Nonetheless, the trial is in equipoise about the effectiveness of the intervention. Trial sites will be randomised 1:1 to either PR-buddy service or to continue delivering care as usual.

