## Intervention

Randomisation will be at the PR-service level. Rates for completion of PR for patient participants who receive PR-buddy support in services in the intervention arm will be compared to those for patient participants in PR services randomised to offer care as usual. Randomisation at the level of sites is essential to prevent contamination of patient participants not receiving the PR-buddy intervention by those who are receiving it or who have received it. For this reason, the comparison will be between sites and not between individual patient participants. Recruitment of patient participants will be identical in both arms of the trial. Patient participants will not be aware of the outcome of the PR service randomisation at the time of recruitment. The site target for recruitment of patient participants, at least 36, will be the same for all sites.

The IMPROVE PR-buddy intervention has five elements: PR-staff training, PR-buddy recruitment, PR-buddy training, patient-participant support by the PR buddies, and PR-buddy management and support by the PR staff. A ‘train-the trainer’ approach will be used, whereby designated PR staff in services in the intervention arm of the trial will be trained in the setting up and running of a PR-buddy service. Using this model moves the burden of training multiple groups of PR buddies from the IMPROVE research team to individual PR services. This will help to provide a more realistic assessment of the intervention as it would be implemented in ‘real-world’ practice and will also facilitate implementation across the NHS if the trial outcome is positive.

The PR-buddy training will be informed by the COM-B model and include selected behaviour change techniques. The COM-B model for behaviour change proposes that there are 3 components to any behaviour: capability (C), opportunity (O), and motivation (M) [28–30]. PR buddies sharing their own positive experiences of PR with patient participants will be a central element of the PR-buddy intervention. Manuals for the training for PR staff and the training of PR buddies will be freely available for services in the NHS only after completion of the trial.

The intervention includes the following steps:

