### Statistical methods for primary and secondary outcomes

Except for enrolled clusters/patients who are found to be ineligible or who withdraw consent at baseline visit and so never receive any treatment, and for whom no data are available, main analyses will be on an intention to treat basis to reflect the randomisation process.

Chi square test adjusting for cluster effect will be used to compare the rates of completion of PR in the two trial arms. Further, a mixed effect logistic model will be used in a sensitivity analysis to adjust for potential confounders, including age, gender and site size. In addition, adjustment for cluster-level variables will be applied for selected variables including site (cluster) size.

The estimates for primary outcome will be presented as odds ratios with 95% confidence intervals for the effect of intervention. Statistical significance will be determined at 5% level using a two-sided test throughout.

A generalised linear mixed model with linear link function will be used to analyse secondary continuous outcome measures. Working correlation matrices will be unstructured, which is not unduly restrictive given that measurements are only taken at three time points. The sandwich estimator of covariance matrix will be used to obtain appropriate (consistent) estimates of precision. Analysis of secondary endpoints will be done at the individual level.

The study has no interim analysis planned.

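### The patient dropout allowance is miscalculated (36 per site covers 16.7% loss, not 20%), and the ICC of 0.056 is not checked against the audit means quoted beside it

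*Protocol article*

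**What the plan says.** The Sample size section starts from a control completion proportion of 40% ("Assuming an overall completion proportion of 40% in the control group") and states that "36 sites (18 per arm) would be required to detect a 40% relative increase in completion proportion to 56% with 90% power". The clustering inputs behind this figure are given as follows: "assuming an intraclass correlation coefficient (ICC) of 0.056 and 30 patient participants per site". It says the same number of sites also serves for 32% rising to 48%. One site per arm is then added, giving 38 sites. Patient dropout is handled in one sentence: "After accounting for six (20%) patient participants dropping out, 36 patient participants would be required in each site". The Intervention section carries that figure into the operational target: "The site target for recruitment of patient participants, at least 36, will be the same for all sites".

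The ICC is attributed to literature and recommendations for similar interventions. The same section reports two audit figures for this outcome: a mean of 40% over 182 sites and, for sites at 55% or less, "the mean completion proportion among these sites was estimated at 32"%. It does not use these to check the ICC, and it gives no between-site SD and no audit site sizes.

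**The concern.** There are two separate issues.

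- **Dropout.** Allowance for a 20% loss means dividing by 0.8. The section multiplies by 1.2, so the stated percentage and the stated target do not match.
- **ICC.** Restricting to sites at or below 55% lowers the mean by 8 points, from 40% to 32%. A drop of that size points to wide variation between sites, wider than an ICC of 0.056 would ordinarily produce.

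At stake is how a null result is read. If the ICC among recruited sites is higher than assumed, the type II error is larger than the 10% that readers will take from the section.

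**Working it through.** **Inputs.** Two-sided 5% ("Statistical significance will be determined at 5% level using a two-sided test throughout"); 1:1 by site ("Trial sites will be randomised 1:1 to either PR-buddy service or to continue delivering care as usual"); 40% v 56% and 32% v 48%; ICC 0.056; 30 per site; 18 sites per arm analysed, 19 randomised; 36 recruited per site.

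**1. Reproducing the plan's figure.**
- Design effect = 1 + (30 − 1) × 0.056 = 2.624.
- Unpooled n per arm for 40% v 56% = 10.507 × (0.24 + 0.2464) / 0.16² = 199.6. Sites per arm = 199.6 × 2.624 / 30 = 17.5, so 18.
- With pooled variance under the null, n is 203 and sites per arm = 203 × 2.624 / 30 = 17.8, so 18. For 32% v 48%: 195 × 2.624 / 30 = 17.1, so 18.
- Power with 18 sites per arm and 30 per site, 40% v 56%: 90.4% (pooled) or 90.8% (unpooled). For 32% v 48%, pooled: 91.5%.

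The plan's figure reproduces in both scenarios.

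**2. Dropout.**
- 6/30 = 20%, but 6/36 = 16.7%.
- 36 × 0.8 = 28.8. To keep 30: 30/0.8 = 37.5, so 38.
- Over 38 sites: 38 × 36 = 1,368 recruited, against 38 × 38 = 1,444.
- With 28.8 per site the design effect is 1 + 27.8 × 0.056 = 2.557, and effective n per arm is 18 × 28.8 / 2.557 = 202.8 (205.8 with 30).
- Power, 40% v 56%: 90.0% (pooled) or 90.4% (unpooled), a loss of about 0.4 points. With a t reference on 36 − 2 = 34 df (unpooled): 88.7%. With all 19 sites per arm, pooled: 91.5%.

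**3. What the audit means suggest.** The site distribution is not given, so its shape is an assumption.
- If the ICC across all audited sites were 0.056, the between-site SD would be √(0.056 × 0.24) = 0.116. The mean at or below 55% would then be about 37.8% under a normal shape, not 32%.
- Normal shape: solving 40 − s·φ(15/s)/Φ(15/s) = 32 gives s = 20.3 points. The SD among sites at or below 55% is 15.1 points, and the ICC is 0.0228 / (0.32 × 0.68) = 0.105.
- Beta shape: SD among those sites 13.3 points, ICC 0.081.
- Beta or logit-normal with binomial noise, assuming 20 to 280 patients per audited site: 0.075 to 0.089.
- Beta, allowing for rounding of the two means: 0.076 to 0.086.

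**4. Power over that range** (28.8 per site, pooled normal reference):

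| ICC | 40% v 56%, 18 per arm | 32% v 48%, 18 per arm | 40% v 56%, 19 per arm |
|---|---|---|---|
| 0.056 | 90.0% | 91.1% | 91.5% |
| 0.075 | 83.9% | 85.3% | 85.8% |
| 0.080 | 82.2% | 83.7% | 84.2% |
| 0.100 | 75.8% | 77.5% | 78.1% |
| 0.105 | 74.3% | 76.0% | 76.6% |

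**The case against.** The case on the other side is substantial.

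- **The calculation works on its own inputs.** It gives 90%, and the dropout slip barely moves it. This stands: every large fall in the table comes from changing the ICC.
- **Two means do not determine an ICC.** Without an assumed shape, the variance among sites at or below 55% has no lower bound above zero. For example, 76% of sites averaging 32% with an SD of 11 points, and 24% averaging 65%, give 0.76 × 32 + 0.24 × 65 = 39.9% overall and an ICC of 0.11² / (0.32 × 0.68) = 0.056 among the lower sites. This stands. A reader might infer that the audit figures imply an ICC of 0.08 to 0.10 and that the trial really has 75 to 83% power. The document does not support that.
- **The audit and trial populations differ.** The Background obtains 40% by combining 62% joining with 65% completing, so it may be a patient-level rate and not a site mean. Participants must also consent and have an mMRC score above 1, and sites may qualify at 65% or less counted from assessment attenders. This stands as a further reason for caution.
- **The denominator matters.** Dividing by 0.40 × 0.60 instead of 0.32 × 0.68 lowers the ICCs to 0.0176/0.24 = 0.073 (beta) and 0.0228/0.24 = 0.095 (normal). This trims the range but leaves it above 0.056.
- **28.8 need not be the number analysed.** Completion comes from site logs, data collected before withdrawal are kept, and missing outcomes are to be imputed. Someone who stops attending is an observed non-completer. This is fair, but the section itself makes a 20% allowance, and that allowance is miscalculated.

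**Conclusion.** The attrition statement is wrong, with certainty: 36 per site allows for 16.7% loss, 20% loss leaves 28.8, and retaining 30 would take 38. The consequence is small, about 0.4 points of power, and it would be wrong to conclude from it that the design misses its target. With a t reference the stated design falls just short of 90%, at 88.7%.

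The ICC point is a matter of support, not of arithmetic. Under ordinary one-peaked site distributions the quoted audit means suggest an ICC of about 0.075 to 0.105 among eligible sites. Power with 18 sites per arm and 28.8 per site would then be about 74 to 84% for 40% v 56%, about 76 to 85% for 32% v 48%, and about 2 points higher if all 19 sites per arm stay. This rests on an assumed shape, on both audit means being site-level means, and on trial sites resembling audited sites at or below 55%. It shows that 0.056 needs checking, not that it is wrong.

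**What to change.** In the Sample size section:

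1. Restate the attrition figure: either 36 per site allows for 16.7% loss, or 20% loss leaves 28.8 analysed per site.
2. Restate power with a t reference on the site degrees of freedom.
3. Check ICC 0.056 against the audit's site-level completion data, limited to sites that would be eligible, and say what was found.
4. Report power over ICC 0.05 to 0.10, labelled as a sensitivity range.

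No sites or patients need be added. The cost is a few sentences and one look at the audit's site-level data; the downside is a slightly less favourable stated power.

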### Recruitment

At time of writing (October 2023), site recruitment is underway. The trial is being promoted in PR services across England and Wales through emails, phone calls, presentations at regional PR-network meetings, meetings with local Clinical Research Networks and conferences. Services interested in becoming a trial site are asked to complete an expression of interest form. PR staff in eligible sites are invited to an information meeting. The expression of interest form and information meeting are used to ascertain if the PR service meets the site eligibility criteria. The IMPROVE trial manager liaises with the local NHS research and development department in relation to assessment of capacity and capability and to get a site agreement in place. A site initiation visit will be held then. The site will be randomised then. All sites will nominate a site Principal Investigator to take overall responsibility for the leadership and conduct of the research at their site.

In sites randomised to the intervention PR staff nominated to undertake the PR-staff training will be consented as trial participants by IMPROVE research staff. Eligible PR buddies will be recruited by the trained PR staff, who will write to COPD patients who have completed PR in their service within the last year. All interested respondents will be screened for eligibility in a phone call. Those considered eligible will then be invited to interview. All those who successfully complete the interview will be invited to attend the PR-buddy training at that site. Consent will be obtained from PR buddies at the first training day.

Patient participants referred for PR will be informed about the trial at the time they are offered a pre-PR assessment appointment. Recruitment and consent of patient participants will be completed by local NHS research delivery staff or local Clinical Research Network staff who are blinded to the outcome of randomisation for the PR service.

### Assignment of interventions: allocation

During the internal pilot, block randomisation will be used. It will be applied to 8 internal pilot sites and will be carried out by the King’s Clinical Trials Unit (KCTU) using specifically designed software. Randomisation data will be held by the KCTU on a King’s College London (KCL) server.

Minimisation randomisation will take place in the main trial also at the level of research (PR) sites. It will be carried out online by the KCTU, also using specifically designed software. Randomisation data will be held by KCTU on a KCL server. Factors in minimisation will be as follows: the workplace setting of the PR service (whether it is a stand-alone PR service or integrated within a respiratory service team or community team); site situation in an urban or rural setting; and delivery of the service in cohorts or as a rolling programme (in cohorts all patients start PR at the same time, in rolling programmes patients can join the programme at any time).

The allocation sequence will be generated by KCTU. IMPROVE research staff will enter the details of the participating sites into the online minimisation randomisation system. The site will then be allocated to either the intervention or control arm of the trial. Back-up telephone access will be available where randomisation cannot be done online. A validated password website using a secure server will ensure concealment.

### Assignment of interventions: blinding

PR staff and PR buddies will know to which arm of the intervention their PR service has been allocated. Patient participants will be blinded until they consent to participate, to ensure their decision to participate is not influenced by whether they will be offered the support of a PR buddy. Staff taking consent from patient participants will not be based in the PR service or the IMPROVE team. These staff will be blinded to the outcome of randomisation until the end of patient-participant recruitment in that site.

Blinding is not related to treatment allocation, but it is important to patient-participant consent. There is no situation in which unblinding would be required for patient safety. Any instances of unblinding of the local NHS research delivery staff or Clinical Research Network taking patient-participant consent will be recorded.

### Data collection and management

Following issue of the greenlight for a site to open the site principal investigator will be asked to provide baseline data for:Number of referrals in the previous 3 monthsProportion of patients invited to PR assessment in the previous 3 months who attended the pre-PR assessment.Proportion of patients who attended PR assessment between 4 and 2 months before this ‘site baseline assessment’ and who then completed PR—that is attended 75% of sessions.

Sites will be provided with logs for the recording of uptake and completion rates of PR by trial patient participants. These logs will include the outcomes of the assessments of exercise capacity at the pre-PR assessment and end of PR assessment (if attended).

Assessment of the delivery and receipt of the PR-staff and PR-buddy training will be based on analysis of recordings of training, checklists of elements of training delivered and training reviews with staff and PR buddies as described above. PR buddies will be lent mobile phones on which to record all interactions with patient participants to allow for assessment of the fidelity of the intervention. They will also be asked to complete logs of contacts with patients they are supporting.

Questionnaires at baseline, 3 and 6 months will provide data for quality of life assessment using the Chronic Obstructive Pulmonary Disease Assessment Test and the Modified Medical Research Council breathlessness questionnaire [36, 38]; anxiety and depression using the Hospital Anxiety and Depression Scale [37]; and a bespoke health resource use evaluation.

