### Methods for additional analyses

Subgroup analyses of the principal outcome measure, completion of pulmonary rehabilitation, are planned to assess the impact of the following: the number of pulmonary rehabilitation sessions attended by patient participants; interval between offer of appointment for pre-PR assessment and first PR class; type of pulmonary rehabilitation programme (rolling or cohort).

Multiple imputation methods will be used, incorporating any available information from the baseline assessment and explanatory variables to impute missing primary or secondary outcome measures. Sensitivity analyses to assess the robustness of the results to various assumptions regarding missing data, or participants lost to follow-up, will be conducted.

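### Each site's pre-trial completion proportion is collected, but it is neither balanced at randomisation nor named in any analysis, and its time window has little margin

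*Protocol article*

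**What the plan says.** All references are to the protocol article.

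- **Data collection and management.** After the greenlight, each site reports its referrals in the previous 3 months, the share of patients invited to assessment in those 3 months who attended, and completion, described as "Proportion of patients who attended PR assessment between 4 and 2 months before this" site baseline assessment and who then attended 75% of sessions.
- **Outcomes.** The trial's own measure is nearly the same: "completion is defined as attendance of 75% or more of the planned PR sessions". The programme is "twelve classes over 6 to 8 weeks and a final assessment", after a pre-PR assessment.
- **Assignment of interventions: allocation.** The pilot sites are block-randomised. The main trial minimises on workplace setting, urban or rural location, and cohort or rolling delivery. Past completion is not a factor.
- **Statistical methods.** The primary comparison is "Chi square test adjusting for cluster effect will be used to compare the rates of completion of PR in the two trial arms". A mixed-effects logistic model is kept for sensitivity, and its stated purpose is to "adjust for potential confounders, including age, gender and site size". On covariates measured per site, the section commits itself only this far: "adjustment for cluster-level variables will be applied for selected variables including site (cluster) size". The effect is to be reported as an odds ratio with a 95% confidence interval.
- **Eligibility and Sample size.** Past completion decides whether a site may enter (at most 55% of appropriate referrals, or at most 65% of assessment attenders). It also supplies the 32% to 40% range for the control arm.

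**The concern.** In a trial of 36 to 38 clusters, variation between sites makes up much of the standard error. A site's earlier completion record is a natural covariate for reducing it, and the trial already collects it. Past completion also governs site entry and the sample size, yet nothing balances it between arms or commits the analysis to allow for it. Two things are at stake: precision, above all if the true ICC exceeds 0.056, and protection against chance imbalance in past performance with about 18 sites per arm.

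A covariate is only as good as its measurement. If some patients in the baseline window are still attending classes when the count is made, the proportion could be too low. The shortfall would be larger at sites with longer waits for a first class, for example where patients wait for the next cohort to start.

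**Working it through.** **1. The plan's own figure.** Inputs from Sample size: 40% v 56%, two-sided 5%, 90% power, ICC 0.056, 30 patients per site.

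- The pooled two-proportion formula without continuity correction gives 203 patients per arm under individual randomisation.
- Design effect = 1 + (30 − 1) × 0.056 = 2.624.
- Sites per arm = 203 × 2.624 / 30 = 17.76, rounded up to 18. This reproduces the plan's 36 sites.
- With 18 sites per arm, the effective size is 540 / 2.624 = 205.8 per arm and power is 90.4%. For 32% v 48% it is 91.5%.

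**2. Effect of adjusting for baseline completion.** Let r be the correlation between a site's baseline proportion and its site-level completion in the trial. Adjustment leaves a residual ICC of about 0.056 × (1 − r²). The protocol gives no r, so a range is shown.

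| r (assumed) | Residual ICC | Design effect | Power, 40% v 56% | Power, 32% v 48% |
|---|---|---|---|---|
| 0 | 0.056 | 2.624 | 90.4% | 91.5% |
| 0.3 | 0.051 | 2.48 | 91.9% | 92.9% |
| 0.5 | 0.042 | 2.22 | 94.5% | 95.2% |
| 0.7 | 0.029 | 1.83 | 97.5% | 97.9% |

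**3. How large r could be.** Sites must offer more than 15 assessments a month, so a 2-month window holds about 30 patients or more. With 30, the reliability of the baseline proportion is 0.056 / (0.056 + 0.944/30) = 0.64. Even if site performance were perfectly stable, r could then not exceed about √0.64 = 0.80. The range 0.3 to 0.7 lies below that ceiling.

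**4. If the ICC is higher than planned.** Take ICC 0.10 (assumed), 18 sites of 30 and 40% v 56%. The design effect is 1 + 29 × 0.10 = 3.9 and unadjusted power is 76%. With r = 0.5 the residual ICC is 0.075, the design effect 3.175 and power 84%. With r = 0.7 these become 0.051, 2.48 and 92%.

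**5. The window.** At 4.348 weeks per month, 2 months is 8.70 weeks and 4 months is 17.39 weeks.

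- Margin between assessment and first class for the latest-assessed patient: 8.70 − 8 = 0.7 weeks for an 8-week programme, and 8.70 − 6 = 2.7 weeks for a 6-week programme.
- With programme length L and wait w in weeks, and assessments spread evenly, the unfinished share of the window is (L + w − 8.70) / 8.70, bounded by 0 and 1.
- No wait: 0% for either length.
- 2-week wait (assumed): 1.30 / 8.70 = 15% for 8 weeks; 0% for 6 weeks.
- 4-week wait (assumed): 3.30 / 8.70 = 38% for 8 weeks; 1.30 / 8.70 = 15% for 6 weeks.
- If every unfinished patient in an 8-week programme were counted as a non-completer, a true 40% would read as 34% (2-week wait) or 25% (4-week wait).

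These are upper bounds. A patient who attends the first 9 of 12 classes qualifies after 4.5 to 6 weeks, which widens the margin to 4.2 and 2.7 weeks respectively.

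**The case against.** **The covariate lists are open.** Both adjustment sentences say that they include the named variables, and the SAP is not shown. A reader might infer that the baseline data go unused; the text supports only that they are not named. This does not dispose of the point, because the open lists belong to the adjusted analyses. The protocol itself fixes the primary test as one without covariates.

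**The gain is hypothetical.** The stated power is reached without adjustment, and r has no source in the protocol. Capping past completion at entry restricts its range, and the Sample size section itself expects regression to the mean; both tend to lower r. At r = 0.3 the gain is about 1.5 percentage points. This stands, and it limits the point to a worthwhile improvement. Nor does the protocol show that past completion is the strongest site covariate, plausible as that is.

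**The window fits the programme.** A reader might infer that a 4-to-2-month window is too recent for a 6-to-8-week course. On the protocol's figures it is not: 8.7 weeks exceeds 8. Truncation needs a wait before the first class, and none is given. The additional analyses list a related but longer interval ("interval between offer of appointment for pre-PR assessment and first PR class") as a subgroup factor, which suggests that waits vary but does not size them. The protocol also does not say how patients still attending are counted. What stands is a thin margin, not a demonstrated error.

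**Timing.** A reader might infer that the baseline is collected after allocation is known. The Recruitment section puts randomisation after the site initiation visit ("The site will be randomised then"), and the baseline request follows the greenlight, but the order of greenlight and randomisation is not stated.

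**Conclusion.** The planned analysis is neither invalid nor underpowered on its own assumptions. It does leave out of its primary test a site-level measure that is close to the outcome, is already being collected and is not balanced by design. At the planned ICC, including it would be worth roughly 1.5 to 7 percentage points of power (90.4% to between 91.9% and 97.5%) for assumed correlations of 0.3 to 0.7. It would be worth more if the ICC were higher, and it would guard against chance imbalance in past completion. The approximation assumes equal site sizes and that adjustment acts only on the between-site variance.

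The window is a secondary matter. Its margin of 0.7 to 2.7 weeks is narrow, but whether any patients are misclassified depends on waits that the protocol does not give.

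**What to change.** 1. **Primary analysis.** Use the mixed-effects logistic model already planned as a sensitivity analysis, or a cluster-level regression, with the site's baseline completion proportion as a prespecified covariate. The mixed model yields the odds ratio that the plan intends to report. Keep the cluster-adjusted chi-square as a supporting analysis. This changes the primary method and is more than an added term, so it should be settled before outcome data are seen. The statistical cost is one degree of freedom among about 36 clusters.
2. **Window.** Move it a few months earlier, so that every counted patient has had time to finish, and anchor it to the randomisation date, so that the same rule applies to both arms whatever the order of greenlight and randomisation. The cost is one extraction per site from routine records; sites already open can do it retrospectively. If the window stays as it is, state how patients still in the programme are counted.
3. **Denominator.** The baseline completion figure is among assessment attenders, while trial patients are approached when an assessment is offered, so the trial outcome can include patients who never attend one. If completed over invited is preferred for that reason, take both counts from the same patients and period. The attendance item now covers invitations in the previous 3 months and the completion item covers assessments 4 to 2 months back, so the two cannot simply be multiplied.
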